For ten years now, our intensive care outpatient clinic has monitored the recovery of patients, especially after long periods of intensive care, and reviewed their experiences during intensive care with patients. Based on our unpublished data, 2-3 months after intensive care, patients report still suffering from many symptoms affecting their quality of life, such as insomnia, nightmares, depression, apathy, exhaustion, and cognitive problems. Memories of delirium are common and disturbing, and going through them with patients is crucially important, and just saying them and declaring them normal helps many. Currently, the intensive care outpatient clinic is temporarily on hiatus due to the challenges brought by the information system change. COVID patients risk missing out on an essential follow-up appointment with an intensive care physician. For this reason, we now want to organize a follow-up outpatient clinic visit as a research project, where we go over issues related to intensive care and his current condition with the patient and, at the same time, investigate neurological and neuropsychological recovery related to long-term recovery from intensive care with clinical tests and imaging methods. The outpatient clinic visit also examines the healing of physical performance, the respiratory system, and immune defenses from a severe illness. It investigates heart symptoms that appeared during or after the disease.

Smells evoke strong positive and negative feelings. Thus, the loss of the sense of smell can significantly worsen the quality of life. Upper respiratory tract infection caused by a virus is the most common cause of loss of sense of smell. During the COVID-19 pandemic, changes in the sense of smell and taste have even been a primary symptom in some of those affected by the coronavirus infection (SARS-CoV-2)^21^. 32-66 % of olfactory disorders after an upper respiratory tract infection recover spontaneously^22^. Olfactory training has been shown to help the sense of smell in recovery^23^. The size of the olfactory coil has been shown to have a predictive value regarding the recovery of the sense of smell^24^. In some patients with coronavirus infection, the sense of smell has recovered within two weeks. Long-term follow-up regarding the recovery of the sense of smell is currently unknown. The study also evaluates whether the continuation of the hyperinflammatory state can be related to prolonged symptoms after COVID-19.

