**II Research questions, hypothesis, research goal**

The study aims to find out (Q=the question layout, H=hypothesis):

1) Q: Do patients treated in the intensive care unit due to the coronavirus show a decline in cognitive performance revealed in extensive neuropsychological tests compared to reference values determined from the general population?

H: Neuropsychological tests show changes in some patients compared to the general population of the same age group.

2) Q: Did any clinically observed neurological complications occur during intensive care?

H: Neurological complications such as delirium and cerebrovascular disorders occurred during intensive care.

3) Q: How have patients recovered from a severe illness neurologically?

H: Most of them have recovered well neurologically, but some may find symptoms in a detailed examination.

4) Q: Does the MRI examination show changes compared to the COVID-19 patients who survived without intensive care treated in the ward?

H: Patients with neurological abnormalities on clinical examination may have radiologically detectable changes on head MRI.

5) Q: Are the patients' neurological symptoms related to white matter damage that could be detected by determining neurofilament levels?

H: Patients with neurological or neurocognitive symptoms can be detected in plasma neurofilament levels compared to non-COVID patients and COVID patients who are neurologically asymptomatic.

6) Q: Is the ApoE4 allele more common in patients with severe Covid-19?

H: In intensive care and hospitalized Covid-19 patients, one or two ApoE4 alleles are detected more often than in patients with Covid-19 at home or controls who have not had a coronavirus infection.

7) Q: Do elevated neurofilament levels and any ApoE allele predict long-term neurological symptoms?

H: Patients with an elevated neurofilament level 6 months after the disease have more neuropsychological changes five years after the infection.

8) Q: Do the patients have a weakening sense of smell or taste compared to the average population 6sixmonths after becoming ill and are there any changes in the neural pathways of the sense of smell on MRI?

H: Some patients have changes in their sense of smell and taste, which have not recovered well or only partially after six months of illness. An MRI examination shows changes in the olfactory nerve or neural pathway.

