We also recruited 50 control subjects who had not had a COVID-19 infection. The table below shows the sub-studies of the study in which these so-called non-Covid controls will be compared to other subjects. The aim is to find non-Covid controls by September 14, 2020, from the close circle of the subjects who gave their consent to the study so that they would be as similar as possible to the subjects treated in the intensive care unit in terms of socioeconomic status and educational level. In practice, the subjects are asked at the follow-up clinic if there are people in their close circle who have not had COVID-19 and whom they would estimate would be willing to participate in the study. They will be forwarded the contact information of the research team so that they can express their interest in the research if they wish. After this, possible non-COVID-19 control subjects will be sent the study information and a consent form in a return envelope.

If enough non-COVID controls are not found through this method, they can also be found among the staff of the University of Helsinki from different professional groups by announcing the recruitment on the University's intranet pages. The aim is to obtain controls from different age and professional groups so that the educational level does not differ significantly from the subjects (who were in intensive care due to Covid).

Patients who give their consent will receive an invitation to come for examination and clinic visits six months after intensive care. Before visiting the outpatient clinic, three months after the disease, the research patients are given a short neurological, and a neuropsychological survey by phone and two questionnaires are mailed to them. More extensive inquiries are made at two separate visits six months after intensive care. The attached table shows the time points and the maps planned for them. At Uppsala Academic Hospital and Oslo University Hospital (if possible), a part of the table will be performed for the corresponding patient groups for the mentioned tests, and the data for them will be combined. mRS, RAND-36, MOCA, and IQCODE tests are conducted in Uppsala. Control patients for the MRI study are searched for using a newspaper advertisement, after which, based on contact, they are asked for informed consent to participate in the study.

Table 1. Tests used in the study, division of labor, time points, and subjects number in HUS. *=Separate consent

| Helsinki |  |  |  |

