| --- | --- | --- | --- |
| Three months | Who makes | Number of patients | Controls |
| Registration of clinical data from patient records (neurological symptoms and examinations during intensive care, delirium, duration of treatment and procedures, background information) | [name] [name] [name] [name] [name] | 100-150 | 50 who were in ward treatment |
| Telephone interview: modified Rankin Scale (mRS) | [name] [name] [name] [name] [name] | 100-150 | 50 inpatients + 50 COVID patients sick at home |
| Telephone interview: Montreal Cognitive Assessment (T-MoCA) | -“- | 100-150 | 50 inpatients + 50 COVID patients who got sick at home + 50 non-COVID controls |
| Behavior Rating Inventory of Executive Function, adult version (BRIEF-A) +BRIEF Informant version ABNAS Neuropsychological questionnaire | by post | 100-150 | ,, |
| Six months | by post |  |  |
| RAND-36 | by post | 100-150 | 50 inpatients + 50 COVID patients sick at home 50 + non-COVID controls |
| MFI-20 | by post | 100-150 | ,, |
| HADS | by post | 100-150 | ,, |
| Informant Questionnaire on Cognitive Decline (IQCODE-CA) | by post | 100-150 | 50 inpatients + 50 COVID patients who got sick at home |
| Behavior Rating Inventory of Executive Function, adult version (BRIEF-A) +BRIEF Informant version | By mail (or NPS in connection with the study) | 100-150 | 50 inpatients + 50 COVID patients sick at home + 50 non-COVID controls |
| Background information | visit (see Visit 1 below) | 100-150 | ,, |
| modified Rankin Scale ( mRS) | visit | 100-150 | ,, |
| Montreal Cognitive Assessment ( MoCA ) | visit | 100-150 | ,, |
| National Institute of Health Stroke Score (NIHSS) | visit | 100-150 | ,, |
| CFS-9 ( clinical frailty scale ) | visit | 100-150 | ,, |
| Olfactory screening test | visit | 100-150 | ,, |
| Follow-up of lung diseases (with the patient's consent, data retrospectively for comparison) | Lung x-ray, spirometry, and diffusion capacity measurement, telephone interview (skin and allergy hospital) | 100-150 | Data from clinical lung function tests of 50 patients who were in ward treatment |
| **Visit 1** |  |  |  |
| Neuropsychological research [name] | Student /[name]/[name]/ [name]/ [name] | 100-150 | 50 inpatients + 50 COVID patients sick at home + 50 non-COVID controls |
| Laboratory samples (immunology) | HUSLAB | 10-50 |  |

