| Brain MRI (ULS) | HUS imaging [name], [name] , [name] | 50 who were in intensive care (at least 30) | 50 inpatients + 50 COVID patients sick at home + 50 non-COVID controls |
| Smell and taste testing | Research nurse | 50 who were in intensive care | -”- |
| **Visit 2** |  |  |  |
| 6-minute walk test | Research nurse, physiotherapist [name] , ERL [name] , LK [name] (6mwt) | 100-150 |  |
| Spirometry and diffusion capacity, meeting with the intensive care physician, reporting the results, and discussing possible further plans | [name], LK [name], [name], / [name] / [name] | 100-150 |  |
| Laboratory samples Fibrosis/inflammation markers Neurofilament + ApoE alleles* | MMP and TIMP-1 analyzes [name] TAU [name] , [name] (University of Gothenburg) [name] | 100-150 | 50 inpatients + 50 COVID patients sick at home + 50 non-COVID controls |
| Method testing of antibody assays Hyyttek , CAT= calibrated automated thermogram , microvesicles, PF4 | [name] [name] [name] [name] [name] [name] (HUSLAB) [name] (HUSLAB) | 100-150 | 50 inpatients + 50 Covid patients sick at home + 50 non-COVID controls |
| 6-12 months |  |  |  |
| Magnetic resonance imaging of the heart | HUS imaging [name], [name], [name], [name], [name] | 50 who were in intensive care, 50 who were in bed ward treatment | 50 non-COVID controls |
| Heart examination laboratory samples P- TnI, Nt -BNP, total blood count, creatinine, ECG | HUSLAB | 50 who were in intensive care, 50 who were in bed ward treatment | 50 non-COVID controls |
| 12 months |  |  |  |
| Antibody assay follow-up samples |  | 100-150 | 50 inpatients + 50 COVID patients who got sick at home |
| 24 months |  |  |  |
| Antibody assay follow-up samples |  | 100-150 | 50 inpatients + 50 COVID patients who got sick at home |
| 6 MW | physiotherapist [name] | 100-150 intensive care patients |  |
| Five years |  |  |  |
| Outpatient visits and neuropsychological testing | Intensive care clinic researchers [name], TBA | 100-150 | 50 inpatients + 50 COVID patients sick at home 50 non-COVID controls |

*Imaging*

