The examination is done in a short version, where a screening test for the sense of smell, testing the smell threshold and testing basic tastes. The research nurse does the testing at the same visit when the MRI imaging is done. The testing uses the smell screening test and the smell threshold testing of the Sniffin'Sticks (level II) test, as well as strip tests for the sense of taste. Contraindications: Known allergy to one of the odorants used and a disorder of the sense of smell diagnosed before the coronavirus infection.

*Pulmonary function and performance*

We ask the patients for consent to use the previous clinical data collected. This data includes possible spirometry and diffusing capacity studies, lung imaging, and clinical information obtained by interviewing the patient. The patients undergo standard spirometry (Pt-FV- SpirD) and diffusion capacity measurement (Pt-Dco-SB1) for the six-month follow-up outpatient clinic visit in the clinical physiology laboratory. At the outpatient clinic visit, a 6-minute walk test and measurement of oxygen saturation without supplemental oxygen are also performed before and after the walk test. Contraindications, 6-minute walk test: Severe heart disease, chest pain or severe shortness of breath during exertion, oxygen saturation in room air before the test < 90%, severe musculoskeletal disease that prevents walking or worsens during work, and febrile infection.

*Blood samples*

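### Hypothesis 8 speaks of smell and taste recovery, but no acute or pre-illness status is named, so the six-month tests support a prevalence comparison and not a recovery statement

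*Protocol*

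**What the plan says.** Question 8 (Section II) asks whether patients have a "weakening sense of smell or taste compared to the average population" at six months, and whether MRI shows changes in the olfactory pathways. The hypothesis goes further: "Some patients have changes in their sense of smell and taste, which have not recovered well or only partially after six months of illness". The Background gives the motive: "Long-term follow-up regarding the recovery of the sense of smell is currently unknown".

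The schedule in Section III, Table 1, is as follows:

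- **Three months:** "three months after the disease, the research patients are given a short neurological, and a neuropsychological survey by phone". The table lists mRS, T-MoCA, BRIEF-A and ABNAS. The record review covers neurological symptoms and examinations during intensive care, delirium, treatment duration and background information. Smell and taste are not named in either.
- **Six months, screening:** "Olfactory screening test | visit | 100-150". Ditto marks give the same three control groups as the rows above it: ward, home-treated COVID and non-COVID.
- **Six months, Visit 1:** "Smell and taste testing | Research nurse | 50 who were in intensive care", with the control groups of the brain MRI row (50 ward, 50 home-treated COVID, 50 non-COVID). The smell and taste section confirms the timing: "The research nurse does the testing at the same visit when the MRI imaging is done".

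Two provisions deal with older loss. The smell and taste section makes "a disorder of the sense of smell diagnosed before the coronavirus infection" a contraindication to the testing. The general exclusion criteria also list sensory impairment, without defining it.

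**The concern.** Recovery describes a course and needs two states: what was lost, and what is present now. The protocol names a source only for the second.

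Other parts of the protocol do supply a reference. Question 13 compares six-month coagulation results with acute-phase samples. The immunology sub-study compares with the acute-phase profile. Hypothesis 9 defines recovery against population reference values. Hypothesis 8 names no reference state for recovery.

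At stake is any statement on how many patients regained smell or taste, wholly or in part. Its denominator would be the patients who lost smell or taste with the infection, and the protocol does not say how they would be identified. Later analysis cannot restore a status that was never asked.

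**Working it through.** No sample size, power or error rate is stated for question 8, so there is no figure of the plan to reproduce. The check is whether the scheduled data identify recovery.

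**1. What one test identifies.** Let L be the share with acute loss, r the share of those who recovered, and b the share with undiagnosed older loss among everyone who is not truly unrecovered. Then

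share low at six months = L(1 − r) + b[1 − L(1 − r)].

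One observed proportion cannot give L, r and b separately.

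**2. The same result fits very different courses.** Suppose, for illustration, that 10 of 50 intensive care patients score low and b = 0. The Background cites 32-66% spontaneous recovery after post-viral loss.

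- r = 0.32: acute loss in 10/0.68 ≈ 15 of 50.
- r = 0.66: acute loss in 10/0.34 ≈ 29 of 50.

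The remaining 40 normal scorers are an unknown mix of fully recovered and never affected.

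**3. Low scores in individuals.** Assumptions not in the protocol: L = 50%, and b = 5% to 25%. Recovery r is taken from the cited 32-66%, with 50% as a value inside it. Per 100 patients:

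| r | Truly unrecovered | Others | Low among others (b = 5% / 25%) | Share of low scorers without unrecovered COVID loss |
|---|---|---|---|---|
| 32% | 34 | 66 | 3.3 / 16.5 | 3.3/37.3 = 9%; 16.5/50.5 = 33% |
| 50% | 25 | 75 | 3.75 / 18.75 | 3.75/28.75 = 13%; 18.75/43.75 = 43% |
| 66% | 17 | 83 | 4.15 / 20.75 | 4.15/21.15 = 20%; 20.75/37.75 = 55% |

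The range is about 9-55%.

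**4. What the non-COVID controls repair.** If their share of low scores estimates the same b, the excess in patients is L(1 − r)(1 − b). With r = 50% and b = 25%, the excess is 43.75 − 25 = 18.75 per 100, and 18.75/0.75 = 25, the true unrecovered count. So the controls remove background loss at group level. They still yield only the product L(1 − r), not the recovery rate r, and they do not classify any one patient.

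**The case against.** The strongest defence is that question 8 is cross-sectional. A comparison with the average population at six months needs no baseline, and tested non-COVID controls are planned. The hypothesis says that some patients have changes, which is a claim of existence, and the protocol nowhere defines a proportion recovered. Hypothesis 9 uses similar language for falling short of reference values, so hypothesis 8 might mean no more than that. All of this stands for the question. It does not fully cover the hypothesis, which names no reference level and speaks of partial recovery, in line with the Background's stated gap.

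A second defence is that silence is not absence. The three-month call has a neurological part, the Ethical considerations section says patients can report bothersome symptoms in it, and background information is collected at six months. Applying the contraindication also implies some check of smell history. Any of these might capture smell status, but the protocol does not say that they do. The record review also does not list the home-treated COVID controls.

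Three stronger readings might be inferred, and the document does not support them:

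- **Patients who never lost smell are counted as non-recovered.** Barring other loss, they would test normal. The confusion is with full recovery.
- **Older loss is uncontrolled.** Diagnosed smell disorders are a contraindication, sensory impairment is excluded, and the controls handle the remainder at group level. What is left is undiagnosed loss in individuals.
- **The MRI part carries the same misclassification.** Question 8 asks only whether pathway changes are present. It states no link between them and recovery status.

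**Conclusion.** The point holds in a limited form. As written, the protocol supports a six-month prevalence comparison of smell and taste with the average population and the non-COVID controls. It does not support a statement on recovery. Full recovery cannot be told from never having been affected, and in an individual a low score cannot be told from undiagnosed older loss.

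The first limitation follows from the schedule and needs no assumed rate. The 9-55% for the second is illustrative: it rests on an assumed 50% acute loss, an assumed 5-25% background, and a recovery range cited for post-viral loss in general. It is not an estimate for this cohort.

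One hypothesis among fifteen numbered aims is affected, and its main question survives. The change is still worth making, because it is cheap and the missing information cannot be recovered at the analysis stage.

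**What to change.** - Add a short smell and taste item set to the existing three-month telephone interview for intensive care, ward and home-treated COVID patients. It should cover status before infection, during the acute illness and now. Repeat it at the six-month visit.
- Report recovery only among those with reported new loss with the infection, and define non-recovery as such a report plus a low six-month test.
- Analyse patients who report loss before infection separately.
- Keep the comparison with the average population and the non-COVID controls as the main analysis of question 8.
- If the items cannot be added, reword hypothesis 8 as a six-month prevalence comparison.

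The cost is three to six questions in a call and a visit that already take place, and a minor amendment. There are two drawbacks. Acute status would rest on recall, which is less reliable in intensive care patients, among whom the Background describes delirium as common and prolonged. The recovery figure would also have a smaller denominator. Patients are identified only after intensive care, so within this study recall or existing records are the only possible sources.

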9) Q: What are the patients' physical performance and lung function parameters 3 and 6 months, and two years after intensive care?

H: In some patients, lung function and physical performance have not recovered to the level of reference values calculated from an average population of the same age.

10) Q: What is the state of the patient’s immune system (is there long-term anergy or other leukocyte dysfunction six months after intensive care)?

H: The functioning of the immune system may still be weakened after six months of illness.

11) Q: Do those iin intensive careor inpatient unit have cardiovascular symptoms?

H: During and/or after the coronavirus infection, there are cardiac symptoms, and they have been more common and continued longer in patients treated in intensive care in demanding patients.

12) Q: Are myocarditis changes visible on magnetic resonance imaging of the heart, and are they present in connection with patients' poorer recovery and cardiac symptoms?

H: Fatigue and slow performance in some patients, especially those who needed intensive care, the background of recovery may be detectable by magnetic resonance imaging sequelae of myocarditis.

13) Q: Can changes in blood clotting factors be seen in Covid-19 infection in sick patients six months after the acute illness phase compared to clinical coagulation factor samples taken in the acute phase?

H: Blood coagulation factors have normalized six months after becoming ill.

14) the partial study investigating SARS-CoV-2 immunity aims to develop tests to measure COVID-19 immunity and bring additional information about the infection immunity and its duration. This is also important for the Covid-19 vaccine in monitoring effectiveness, as the test can be used to measure the vaccine separately induced and infection-induced immune response.

15) Q: Can elevated MMP -7, -8, or-9 concentrations or cytokines or tissue inhibitors involved in their regulation have abnormal concentrations, and whether the potentially elevated levels are associated with clinical symptoms and findings, e.g., lung function or imaging?

H: In some patients who are still severely symptomatic, there are elevated levels of inflammatory markers. The goal is to characterize the patients' long-term recovery and, if necessary, refer the patients to appropriate follow-up examinations or rehabilitation.

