**Exclusion criteria:**

-pregnancy

- a significant neurological disease diagnosed before the coronavirus infection, such as a severe one

the aftermath of a brain injury or cerebrovascular accident

-sensory impairment

- memory disorder

-Parkinson's disease

-disability

Section-specific exclusion criteria, if any, are listed in connection with the description of each study section. The assumed number of patients is around 100-150. Patients are identified after intensive care using a registered COVID-19 diagnosis from the intensive care quality database, after which they are contacted and asked to participate in the study. Patients are sent a *Patient and Next of kin Research Information Sheet* and a consent form with the contact information of the research team for further details. For the continuation of the study, new information about the subject and consent forms will be sent to the subjects by post, or their consent will be asked when meeting them at the follow-up clinic. Among the research subjects, there are only people who use Finnish as their business language, so the research documents for further research have only been prepared in Finnish.

Control patients are recruited through a newspaper advertisement and with the help of social media. Control patients are persons with a confirmed coronavirus infection whose severity of illness did not require intensive care, but the disease was contracted at home (N=50). Another control group, patients who received treatment for coronavirus infection in a hospital bed ward (N=50), will be identified to ask for consent from those who receive/are receiving an invitation to a follow-up organized by the lung disease clinic. Separate written consent to participate in the study is requested from the control persons.

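### Hypothesis 11 compares the frequency and duration of cardiac symptoms in ICU and ward patients, but Table 1 schedules no cardiac-symptom measure for any group

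*Protocol*

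**What the plan says.** Section II, question 11, asks whether those treated in the ICU or the "inpatient unit have cardiovascular symptoms". The hypothesis goes further: "there are cardiac symptoms, and they have been more common and continued longer in patients treated in intensive care". The end of that sentence is garbled in the text at hand, so the ward group is taken as the comparator from the question. Question 12 then asks whether cardiac MRI changes go with poorer recovery and cardiac symptoms.

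Section I says of the follow-up outpatient visit: "It investigates heart symptoms that appeared during or after the disease". It introduces that visit as a replacement for the intensive care clinic appointment that patients would otherwise miss. No instrument is named.

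Table 1 in section III sets out what is collected. The rows that bear on this point are:

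- Three-month record review, ICU and ward: "Registration of clinical data from patient records (neurological symptoms and examinations during intensive care, delirium, duration of treatment and procedures, background information".
- Visit 2 physician contact, 100-150 patients, controls cell empty: "meeting with the intensive care physician, reporting the results, and discussing possible further plans".
- Cardiac session at 6-12 months: MRI, and "Heart examination laboratory samples P- TnI, Nt -BNP, total blood count, creatinine, ECG", for "50 who were in intensive care, 50 who were in bed ward treatment", with 50 non-COVID controls.

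**The concern.** The hypothesis is comparative on two features, how common the symptoms are and how long they last. Both have to be recorded in both groups by the same method. If no form is scheduled, the data will come from whatever the clinical contacts happen to note, and the scheduled physician contact is listed for ICU patients only. More questioning finds more symptoms, so the likely error runs in the direction of the hypothesis.

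An analysis plan cannot repair this, because it cannot analyse a variable that was not collected. Question 12 needs the same variable to relate MRI findings to cardiac symptoms.

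**Working it through.** **Step 1. Go through Table 1 for a cardiac-symptom item.**

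| Time | Scheduled for ICU patients | Also for ward patients? | Cardiac-symptom item named? |
| --- | --- | --- | --- |
| 3 months | Record review (neurological symptoms, delirium, treatment, background) | Yes | No |
| 3 months | Telephone mRS and T-MoCA | Yes | No |
| 3 months | Postal BRIEF-A and ABNAS | Yes | No |
| 6 months | Postal RAND-36, MFI-20, HADS, IQCODE; BRIEF-A by mail or at the neuropsychology visit | Yes | No |
| 6 months | Visit: background information, mRS, MoCA, NIHSS, frailty scale, smell screening | Yes (ditto marks) | No |
| 6 months | Lung follow-up, including a telephone interview | Existing lung function data only | No |
| Visit 1 | Neuropsychology, brain MRI, smell and taste testing | Yes | No |
| Visit 1 | Immunology samples | Controls cell empty | No |
| Visit 2 | Walk test; spirometry with physician meeting | Controls cell empty | No |
| Visit 2 | Research blood samples | Yes | No |
| 6-12 months | Cardiac MRI, blood samples, ECG | Yes | No |
| 12 and 24 months | Antibody samples | Yes | No |
| 24 months | Walk test | Controls cell empty | No |
| 5 years | Outpatient visit, neuropsychology | Yes | No |

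The text on cardiac imaging and on the same-day blood samples in section III adds no symptom inquiry.

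**Step 2. Locate the inquiry that is described.** The section I sentence ties it to the outpatient clinic visit. The row that most resembles that visit is the Visit 2 physician meeting, which has no ward patients. The link between the two is a reasonable reading, but the protocol does not state it.

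**Step 3. Illustrate what unequal recording would do.** The protocol gives no symptom rate, recording rate, alpha or power for question 11, so there is no figure to reproduce. Everything here except the group sizes is an assumption.

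Inputs: true prevalence p = 30% in both groups; share of symptoms recorded 90% in ICU patients and s in ward patients; ICU n = 50 to 150, ward n = 50; two-sided alpha 0.05.

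Observed rates are 0.90p and s·p, so the apparent risk ratio is 0.90/s whatever p is. The chance of a significant result in favour of ICU patients is about Φ((d − 1.96·SE0)/SE1), where d is the difference in observed rates, SE0 uses the pooled rate and SE1 the separate rates. For s = 70% and 50 per group: d = 0.27 − 0.21 = 0.06, SE0 = √(0.24 × 0.76 × 2/50) = 0.0854, SE1 = √(0.27 × 0.73/50 + 0.21 × 0.79/50) = 0.0852, giving Φ(−1.26) = 10.4%.

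| Ward recording s | Observed ICU / ward | Difference | Risk ratio | Chance of significance (ICU n 50-150) | Same, p from 20% to 40% |
| --- | --- | --- | --- | --- | --- |
| 90% (equal) | 27% / 27% | 0 | 1.0 | 2.5% | 2.5% |
| 70% | 27% / 21% | 6 points | 1.29 | 10-12% | 8-17% |
| 50% | 27% / 15% | 12 points | 1.8 | 31-39% | 21-56% |
| 30% | 27% / 9% | 18 points | 3.0 | 65-80% | 45-94% |

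If nothing at all is recorded for ward patients, there is no comparison to bias.

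**The case against.** A reader might infer that the schedule has ICU patients asked about their hearts by a physician and ward patients not asked at all, so that unequal questioning will by itself confirm the hypothesis. The document does not support that.

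- No cardiac-symptom instrument is named for ICU patients either. The Visit 2 row speaks of results and plans and does not mention the heart, and the section I sentence names neither a questioner nor a form. What the text establishes is that the measurement is unspecified in both groups.
- Ward patients do have contacts where symptoms could come up: the background-information item at a visit, and the three-month call, in connection with which section VI says patients can mention troublesome symptoms. Neither is described as recording cardiac symptoms, and volunteered complaints are not a measurement, but silence is not proof that nobody asks.

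A reader might also infer that duration cannot be estimated because there are no repeated measurements. Recalled onset and end at a single contact would give a duration. The gap is that no item is scheduled to obtain them.

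Finally, the cardiac MRI, troponin, BNP and ECG are scheduled alike for ICU, ward and non-COVID subjects, and the fatigue scale goes to ICU and ward patients alike. That protects the objective side of question 12 and its interest in fatigue. It does not supply symptoms, which are what question 11 is about.

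What stands after this is the absence of any scheduled variable, together with a risk of unequal ascertainment if clinic notes are used in its place.

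**Conclusion.** The point holds in this form: followed as written, the protocol yields no standardised cardiac-symptom variable collected in the same way from ICU and ward patients. Question 11 and the symptom part of question 12 have nothing comparable to rest on. This follows from Table 1 and needs no assumption.

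The bias is a risk and its size cannot be derived from the document. Its direction, towards the hypothesis, rests on reading the section I inquiry as taking place at the Visit 2 physician meeting. The table in the working depends wholly on assumed prevalence and recording rates: at 70% ward recording the effect is modest, and the large effects need ward recording of about 30%.

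**What to change.** Add one row to Table 1 for a short structured cardiac-symptom form, for example chest pain, palpitations, exertional breathlessness and syncope. Score each item as present before the infection, during the acute illness and now, with onset and end. Give it to ICU and ward patients in identical wording and by the same mode, at contacts both groups already have. There are two options:

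- **The three-month call and the six-month mailing.** These reach all 100-150 ICU patients and the 50 ward patients. The six-month mailing also reaches non-COVID controls, for a background rate.
- **The cardiac MRI day.** All three groups attend, and symptoms would be recorded on the same day as the ECG and blood samples. It covers only 50 of the ICU patients, leaves out those excluded from cardiac MRI, and comes later.

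State that question 11, and the symptom part of question 12, use this form only and not notes from the physician meeting.

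The cost is a protocol amendment and a few minutes per respondent, with no new visit. Acute-phase symptoms would rest on recall, which may itself differ between ICU and ward patients. The three-month call shortens the recall interval and is the better choice where it is still possible.
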